### Measures

Questionnaires and interviews are administered to the families in six waves, in addition to the weekly PATH questionnaire which is filled out by children (above the age of 8 years), parents and MATCH therapists between each session throughout the course of treatment. Therapists, supervisors, and team-leaders at each clinic also fill out questionnaires. See Fig. 1 and the description of measures for details. The pre-assessement (T1) is administered after receipt of consent and prior to randomization. At 3 and 6 months (T2 and T3, respectively) into treatment, a short assessment is administered to children and parents, and these are both time-invariant and thus occur at the same time for all families enrolled, regardless of group assignment or treatment progress. Shortly after treatment has concluded, families fill out the post-assessment (T4). The time at which the post-assessment is administered varies among families depending on how long the treatment period has lasted, and so this assessment is time-varying. At 15 months (T5) after treatment initiation, another short assessment is administered. The last assessment (T6), the follow-up, is administered 1 year after the end of treatment, and so is time-variant relating to T1 (because it depends on how long treatment lasted), but is time-invariant in relation to T4 (because it is carried out 1 year post treatment conclusion)

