### Design and power

The trial is a randomized controlled effectiveness trial conducted in existing child and adolescent outpatient clinics in Norway. Participants are randomized within each site, following a computer-generated list with each participant having a 50% chance of being assigned to either group. The results of the randomization are provided to the clinic for each new case. The process is as follows:*Referral*: children and their families are referred to the participating clinics (primarily by either their general physician, head of the municipal child welfare agency, or community psychologist) for child symptoms of anxiety, depression, trauma-related problems and/or conduct problems. Children and families are assessed for eligibility for the study based on these referral reasons, and on whether they have significant symptom levels meeting study cut-offs at the time of screening (see item c and “Rationale for the use of cut-off scores” below)*Consent*: once found eligible at this stage, families are informed of the trial by the contact person at the clinic. If the family consents, their contact information is given to the Norwegian Center for Child Behavioral Development (NCCBD) which then registers the information and contacts the family to provide more information about the trial and to ask whether the family wants to participate. The family is informed briefly about the treatment options and that random assignment is involved. If the family agrees, a consent letter, along with a brief study description (including contact information of the study personnel), is sent to the family. The NCCBD then registers receipt of a signed consent from the family. A phone call is made to the family within a few days to make sure that they have received the letter in the mail. If the NCCBD has not received a signed consent within 2 weeks, another phone call is made to the family, to allow for questions and to urge interested families to sign and send in the consent form.*Pre-assessment and decisions about inclusion to the trial*: upon receipt of a signed consent form from the family, the pre-intervention assessment (wave 1) is sent out to the family This is done approximately 2 weeks prior to the date set for their first consultation at the clinic. A reminder is sent out to the family after 1 week, and is followed up by weekly phone calls if they have not submitted the completed assessment. The pre-intervention assessment, on which scores are based to assess eligibility to the trial, include the CBCL, YSR, KATE and if relevant (given the scores on the KATE), the child and parent version of CATS. Children between the ages of 8 and 11 years complete these questionnaires at the clinic together with a clinician. The family is eligible if the child’s scores are at or above clinical cut-off scores.*Further assessment by the clinics and setting the primary protocol*: the clinics receive the summary scores on the CBCL, YSR, KATE, and CATS from the NCCBD. In some cases, the clinics administer these questionnaires directly to the families as part of their routine, and in these cases, the NCCBD receives the results from the clinic(s), after collected consent. For children with T-scores above the cut-off, a therapist at the clinic conducts a TPA. Based on the result from these assessments, MATCH consultants make the decision about the child’s primary protocol to be tried first (primary problem area). MATCH consists of four treatment protocols, one for each problem area; anxiety, depression, trauma, and conduct problems*Randomization*: once inclusion to the study and primary protocol are determined, the family is randomized to either the MATCH condition or the TAU condition. Information about the outcome of the randomization procedure is then provided to the clinic. The outcome of the randomization then triggers two events: (1) the dates for the time-invariant assessment points (i.e., the 3-, 6-, and 15-month assessments) and (2) the clinics being alerted to inform the NCCBD of who the therapist for the family will be, along with their contact information*Registration in PATH*: families are then added to the PATH system a week prior to their first meeting with their appointed therapist. The families receive an email on the Sunday of each week asking the parent and the child (if they are over 8 years old) to fill out a questionnaire, consisting of the TPA and the BFS. The TPA and the BFS are collected weekly (or between each session) as part of the PATH system of user feedback

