#### For main effects

The time-variant assessments, that is, the pre-, post-, and follow-up assessments, will be analyzed using descriptive statistics and general linear models (GLM), controlling for age, gender, type of problem area, and family background information (e.g., SES).

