### Sample size

#### The number of subjects planned to be enrolled

We plan to recruit 280 children and their families. Based on a power analysis for the analysis of main effect, we concluded that a sample size of 280 will detect an effect size of 0.3, provided power of .80, at an alpha level of .05.

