#### The selection of participants to be included in the analyses

We will answer two important research questions: First, to answer the question of “Does MATCH work?” we will employ a per-protocol design; thus only those children and families who have gone through treatment will be included. Second, the question of whether “MATCH makes a difference in existing clinics” is best approached via an intention-to-treat design (ITT), in which all families randomized will be included in the analyses, regardless of whether they entered or completed treatment. Thus, we will analyze data using both ITT and per-protocol designs in an effort to answer these two overall questions.

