#### Data Monitoring Committee (DMC)

This study is an effectiveness trial, conducted in existing child and youth mental health clinics, not in a research facility. The intervention is psychotherapeutic and is considered low risk and no more intrusive than what is being delivered to children and families in the clinics as part of their regular treatment delivery. The participating clinics have internal procedures for detecting, reporting, and following up on any adverse events in their patients. The study does not pose any restrictions on the clinics’ internal procedures for handling adverse events or from offering another treatment if deemed appropriate. In the event of the clinic terminating a MATCH treatment, the research team at the NCCBD will be informed, and post-assessment will be conducted. The trial is not blinded, as the therapists know what kind of treatment they offer the children and their families. MATCH therapists are routinely guided by US consultants with follow-up assistance from Norwegian co-consultants throughout the treatment. Interim analyses will not be conducted, in order not to bias the progression of the study.

Carandang et al. [5] reported on a set of issues to consider for mental health researchers when deciding whether to appoint a DMC for a mental health study. These issues included (1) risk of the psychiatric disorders (e.g., suicidal risk), (2) features of treatment (whether it is pharmacological), (3) research environment (extend of experience), (4) lack of information on the study population (e.g., comorbidity), and (5) lack of information about the treatment (e.g., novel and without prior results). The study population in the current study can certainly be considered vulnerable; however, information about suicide attempts (and suicidal ideation) and psychosis are collected and excluded from participation, the intervention is psychotherapeutic and is considered low risk, and the research environment consists of experienced researchers who have conducted several randomized trials with similar populations of children and youth. The researchers and the treating therapist(s) know a great deal about the children and their family. The intervention consists of known and well-tested treatment components, and it has been implemented in other settings with promising results. For these reasons, the current study has not appointed a DMC.

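### The promised ITT analysis includes families who never start treatment, but the main-effect outcomes at T4 and T6 have no date for such families

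*Protocol article*

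**What the plan says.** Four parts of the protocol article bear on this.

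- **Population.** The section on the selection of participants plans both a per-protocol and an ITT analysis. The ITT analysis is one "in which all families randomized will be included in the analyses, regardless of whether they entered or completed treatment".
- **Model.** Under the heading for main effects, the pre-, post- and follow-up assessments "will be analyzed using descriptive statistics and general linear models (GLM), controlling for age, gender, type of problem area", together with family background.
- **Outcome times.** Under Measures: "Shortly after treatment has concluded, families fill out the post-assessment (T4"). T6 "is administered 1 year after the end of treatment". Both therefore depend on a treatment having ended.
- **Treatment that ends abnormally.** The section on the data monitoring committee says: "In the event of the clinic terminating a MATCH treatment, the research team at the NCCBD will be informed, and post-assessment will be conducted".

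The 3-, 6- and 15-month assessments (T2, T3, T5) are handled separately. Design and power has randomisation trigger their dates, and the section on time-invariant assessments assigns them, with the pre-assessment and the PATH data, to mixed-effects and growth curve models.

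**The concern.** The population, the model and the outcome times are each stated, and they do not fit together for one group. The ITT definition expressly expects families who never enter treatment. The main effect is estimated at two time points that exist only for families whose treatment has ended. A never-starter has no end of treatment, so no post-assessment is due and no follow-up can be counted from it.

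The first and third research questions, posed at post-treatment and at one-year follow-up, rest on T4 and T6. The article uses ITT to ask whether MATCH makes a difference in existing clinics, and never-starters are part of that question. If they fall out, the estimate describes families who began treatment. If failure to start or capture of T4 differs between arms, the comparison is no longer fully protected by randomisation. The second possibility has some support in the text, because the one rule that secures a T4 after an abnormal ending names MATCH only.

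**Working it through.** **Which families have a dated outcome**

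| Family | T4 and T6 | T2, T3, T5 if dated from randomisation |
|---|---|---|
| Completes treatment, either arm | Dated | Dated |
| Starts MATCH, clinic ends it | Dated; post-assessment expressly required | Dated |
| Starts TAU, stops early | Dated from end of treatment; no express rule | Dated |
| Never starts, either arm | No date | Dated |

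Only the last row lacks T4 and T6 by construction. Missing T4 in the other rows is ordinary non-response.

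**Which primary questionnaires the fixed waves can carry**

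- Parent CBCL internalizing and externalizing: collected at T2, T3 and T5.
- Parent CATS: collected at every wave where the trauma index indicates it.
- YSR: pre, post and follow-up only. Child-reported CATS is likewise absent from T2, T3 and T5.

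The fixed waves therefore give a route to ITT for the parent measures and none for YSR.

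**Whether the fixed waves really are dated for never-starters**

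Design and power has the outcome of randomisation set the dates. Measures counts T2 and T3 from within treatment and T5 from treatment initiation, yet also says that they fall at the same time for all families. Only the first reading gives never-starters a date.

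**The plan's sample size**

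Inputs: "a sample size of 280 will detect an effect size of 0.3, provided power of .80, at an alpha level of .05", and "each participant having a 50% chance of being assigned to either group", so 140 per arm. The standard deviation is 1 because the effect is standardised. Sidedness is not stated, so both are tried.

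n per arm = 2(z_α + z_0.80)² / d²

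- One-sided: 2(1.645 + 0.842)² / 0.09 gives 138 per arm, 276 in total. This is close to 280.
- Two-sided: 2(1.960 + 0.842)² / 0.09 gives 175 per arm, 350 in total. This does not reproduce 280.

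A two-sided 280 would reproduce if covariates explained about 20% of outcome variance (1 − 140/174.4 = 0.197), which the article does not state. The one-sided requirement of 276 against 280 leaves almost no room for loss.

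**Power if never-starters are omitted**

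Power = Φ(d·√(m/2) − z_α), with m analysed per arm. The loss is assumed and equal in both arms.

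| Assumed loss | N analysed | One-sided | Two-sided |
|---|---|---|---|
| 0% | 280 | 0.807 | 0.709 |
| 5% | 266 | 0.789 | 0.687 |
| 10% | 252 | 0.769 | 0.663 |
| 20% | 224 | 0.726 | 0.612 |
| 30% | 196 | 0.675 | 0.556 |

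Example at 10%, two-sided: m = 126, 0.3·√63 = 2.381, 2.381 − 1.960 = 0.421, Φ = 0.663.

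Only the fall within a column belongs to this point. At 10% that is 0.038 one-sided (0.807 − 0.769) or 0.046 two-sided (0.709 − 0.663).

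**The case against.** The strongest reply is that naming a GLM is not a commitment to complete cases. A GLM can be fitted after multiple imputation, and the handling of missing outcomes commonly sits in an analysis plan or full protocol that is not shown. That stands: a reader might infer that a GLM cannot deliver ITT, and the article does not support this. Imputation, however, does not say when the missing value was due, and the article itself fixes outcome times that leave never-starters without one.

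Secondly, the ITT promise is not tied to the GLM alone. The article plans several analyses, and mixed models on the fixed waves already offer an ITT route for parent CBCL. This stands in part. The article assigns those models to trajectories of change, not to the main effect at post-treatment and follow-up, and they do not reach YSR.

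Thirdly, a reader might infer that the ITT analysis collapses into the per-protocol one. It does not. Families who start and stop early have an end of treatment and hence a T4, and they can remain in the GLM while falling outside the per-protocol set.

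Fourthly, a reader might blame this fault for the gap between the stated power of 0.80 and 0.71 at the full 280. That gap comes from assuming an unadjusted two-sided test and is a separate sample-size matter.

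Finally, modelling time since randomisation moves away from research questions posed at the end of treatment. That is true and is a real cost of the fix.

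**Conclusion.** The point holds in a limited form. As written, the article promises to analyse families who never enter treatment, and it bases the main effect on outcomes that are undefined for them. A GLM on observed T4 or T6 omits them. The rule securing a post-assessment after an abnormal ending covers only MATCH treatments ended by the clinic, so T4 capture could differ by arm; the article does not show that it will.

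The size is unknown. No share of never-starters is given, and the 5% to 30% range above is an assumption with equal loss in both arms. No direction or size of bias can be derived from the document. The main harm is to what is estimated rather than to power: bringing never-starters back restores the randomised comparison but need not restore power, because families who received no treatment may show little difference between arms.

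The fault lies in the outcome times more than in the GLM. Changing the model alone would not define T4 or T6.

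**What to change.** 1. Make the ITT comparison for parent CBCL and parent CATS a likelihood-based mixed model, a class that the article already names. Use all available waves of every randomised family, with time measured from randomisation and the covariates listed for main effects. Keep the GLM on T4 and T6 as a supporting analysis.
2. In both arms, set T4 and T6 assessment dates for families who never start, at a fixed time after randomisation stated in advance. YSR needs this in any case, because the fixed waves do not collect it.
3. Reconcile Measures with Design and power on whether T2, T3 and T5 are counted from treatment start or from randomisation. Step 1 depends on the second reading.

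The cost is slightly more analysis work, a few added assessment dates, and an ITT estimate referenced to time since randomisation rather than to the end of treatment. Recruitment began in March 2016, so some never-starters may already be past any date that is set. For them the mixed model can still use whatever parent data the fixed waves hold, but a missed YSR cannot be recovered.

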#### The Achenbach System of Empirically Based Assessment (ASEBA; CBCL and YSR)

The child’s behavior and symptomology are assessed by multi-informant ratings from caregivers and children on the CBCL [1] and YSR [1], respectively. This family of measures is one of the most widely used to assess child and adolescent emotional and behavioral functioning and has been validated in numerous studies (e.g., [12]). The instruments assess a broad array of behavioral and emotional manifestations of psychopathology, yielding eight syndrome scales of which the broad band scales “Internalizing” and “Externalizing” will be of particular importance in this study. CBCL and YSR are administered at the pre-, post-, and follow-up assessments. Parents also complete the internalizing and externalizing sub-scales of the CBCL at the 3-, 6-, and 15-month assessment points (waves 2, 3, and 5).

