#### Level of significance to be used

In most analyses, a significance level of α = .05 will be used for main effects analyses, mediation models, growth curve models, and general models of association. We will use more stringent alpha levels in subsequent analyses in cases where many variables are entered into prediction models, to reduce the risk of Type 1 error.

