#### The number of participants projected at each site

The number of families to be recruited at each site was calculated based on the number of therapists trained at each site, with the expectation that each MATCH therapist would contribute with at least six cases each to the study, matched by an equal number of cases from TAU therapists. Six clinics participate at the present. Originally, one more outpatient clinic was recruited to take part in this trial. In the fall of 2016, however, it became clear that this clinic was not able to fulfill the requirements of participation and was, therefore, excluded from the trial, from therapist consultation, from the use of the PATH system, and all other MATCH elements. This decision was reached in agreement with the management at the clinic in question. We had originally planned to recruit 36 families from this site. Thus, the remaining six clinics have been asked to recruit, between them, the remaining families to compensate for the loss. As of fall 2017, we are in the process of recruiting two or three more clinics.

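### The main-effects covariate list leaves out the randomisation site and does not fix the role of the T1 score, so precision may be lost on data already collected

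*Protocol article*

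**What the plan says.** The section on main effects applies general linear models to the pre-, post- and follow-up assessments, "controlling for age, gender, type of problem area, and family background information (e.g., SES". No other part of the statistical analysis section adds to this list. The mixed-effects and growth-curve models are reserved for the pre, 3-, 6- and 15-month data and the weekly PATH data.

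On the design, "Participants are randomized within each site" (Design and power). Site is the only randomisation stratum stated. On clinic numbers, "Six clinics participate at the present", and two or three more are being recruited.

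On baseline, "The pre-assessement (T1) is administered after receipt of consent and prior to randomization" (Measures), and "CBCL and YSR are administered at the pre-, post-, and follow-up assessments" (ASEBA section). CATS differs: it is completed only if the trauma-event index KATE is positive. The first research question under Aims compares the arms on symptom level at post-treatment.

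On size, the article says that "a sample size of 280 will detect an effect size of 0.3, provided power of .80, at an alpha level of .05".

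**The concern.** The article does more than name a model family; it gives a covariate list. Two variables that one would expect there are not on it: the stratum of the randomisation, and the pre-randomisation value of the scale being analysed.

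The pre-assessment does appear in the same sentence, as one of the assessments to be analysed, but its role is open. Three models fit the wording:

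- the post score alone, with the listed covariates;
- a pre-post change or group-by-time model, with T1 as a repeated outcome;
- the post score with T1 as a covariate.

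The first two are less precise than the third, and only the third makes full use of a T1 score that is already collected. Leaving the choice open also means that it could be made after the data are seen.

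**Working it through.** **Inputs from the article.** Total N = 280. Allocation is 1:1 ("each participant having a 50% chance of being assigned to either group"), so 140 per arm. The effect size of 0.3 is read as a standardised mean difference with SD = 1. For alpha, "a significance level of α = .05 will be used for main effects analyses"; sidedness is not stated.

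**Inputs assumed.** The T1-outcome correlation r is set at 0.3, 0.5 and 0.6, and the share of outcome variance lying between sites at 1%, 5% and 10%. The article gives neither. Variances at T1 and post are taken as equal, there is no dropout, and the covariates already listed are taken to explain none of the outcome variance.

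**The plan's own figure.** n per arm = 2(z_alpha + z_power)²/d².

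- One-sided: 2(1.645 + 0.842)²/0.09 = 137.4, so 138 per arm and 276 in total. Power at 140 per arm is 0.807. This matches the stated 280.
- Two-sided: 2(1.960 + 0.842)²/0.09 = 174.4, so 175 per arm and 350 in total. Power at 140 per arm is 0.709. This does not match.

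Without covariate adjustment, the 280 is therefore reproduced only by a one-sided test. The comparison below uses the two-sided test.

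**Effect of T1's role.** Power = Φ(0.3/(s·√(2/140)) − 1.960), where √(2/140) = 0.1195. The residual SD s depends on the model:

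- post-only: s = 1;
- pre-post change or group-by-time: s = √(2(1 − r));
- T1 as covariate: s = √(1 − r²).

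Worked case at r = 0.5 with T1 as covariate: s = √0.75 = 0.866; 0.3/(0.866 × 0.1195) = 2.898; 2.898 − 1.960 = 0.938; Φ(0.938) = 0.826.

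| Assumed r | Post-only: power (total N for 80%) | Change: power (N) | T1 covariate: power (N) |
|---|---|---|---|
| 0.3 | 0.709 (350) | 0.564 (490) | 0.749 (318) |
| 0.5 | 0.709 (350) | 0.709 (350) | 0.826 (262) |
| 0.6 | 0.709 (350) | 0.801 (280) | 0.881 (224) |

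The ranking does not depend on the r chosen. Against post-only, the covariate model multiplies the standard error by √(1 − r²): 0.954, 0.866 and 0.800. Against the change model it multiplies it by √((1 + r)/2): 0.806, 0.866 and 0.894. Both factors are below 1 for any r between 0 and 1. Below r = 0.5 the change model is less precise than ignoring T1 altogether.

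With T1 as covariate, 280 reaches two-sided power of 0.80 at r = √(1 − 140/174.4) = 0.444.

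**Effect of site.** Removing the between-site share gives s = √(1 − share). From the post-only 0.709, power rises to 0.713 (1%), 0.731 (5%) and 0.754 (10%), a gain of about 0.4 to 4.5 percentage points.

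**The case against.** The strongest reply is that the article does not leave T1 out: the pre-assessment is named among the data that the model analyses. That is correct. A reader might infer from the covariate list that T1 is ignored, but the text shows only that its role is not fixed. If it was always meant as a covariate, the T1 part of the loss disappears.

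A second reply is that a condensed article may leave such detail to the analysis plan. This would carry more weight if no covariates were listed. Here they are listed, and site does not appear there or anywhere else in the analysis section.

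Several further limits stand:

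- The list is not purely demographic. Problem area is clinical and is set after the T1 scores are known, so it may already carry some T1 information. The gains above, which give the listed covariates no explanatory value, may then be too large.
- Children are selected on T1 cut-offs. This restricts the T1 range and tends to lower r.
- A reader might infer that omitting site invalidates the standard error. That depends on balancing within site, and the article states only a computer-generated list with an even chance, not blocking. Under simple randomisation within site the unadjusted standard error is not invalid. Under blocking, omitting site typically makes the test conservative.
- T1 scores do not exist for every child on every scale. A child with a negative KATE has no T1 CATS score.

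**Conclusion.** The point holds as a loss of precision and a mismatch with the design. Randomisation protects the estimate, so a claim of bias is not supported; chance baseline imbalance is random error.

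At an assumed r of 0.5, fixing T1 as a covariate raises two-sided power from 0.709, under either alternative reading, to 0.826. Over r from 0.3 to 0.6 the gain is 0.040 to 0.172 against post-only (0.749 − 0.709; 0.881 − 0.709). Against a change model it is 0.185 at r = 0.3 and 0.080 at r = 0.6 (0.749 − 0.564; 0.881 − 0.801). The size rests on assumed correlations; the direction does not.

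The gain from site is modest and also rests on assumed shares. The better reason for including it is that the analysis should reflect how families were randomised.

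The missing sidedness is a separate matter of the sample-size statement and does not change the ranking of the models.

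**What to change.** State that each post and follow-up score is modelled with its own T1 score and with site as a fixed effect, in addition to age, gender, problem area and family background. If a repeated-measures model is preferred, constrain the arms to a common mean at T1 and include site.

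For CATS, apply the T1 covariate where a T1 score exists, and state in advance how children without one (negative KATE) are handled.

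The cost is small: one sentence for CBCL and YSR and one more for CATS, with no new data, visits or families. Site uses 5 degrees of freedom with six clinics (6 − 1), or 8 if three more join (9 − 1), which is negligible against 280 children.
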